### 2.11. Study Instruments

The study collects data from existing registries as well as through questionnaires:The Ugandan VHT household register (VHTR): This will be the entry basis into the community for both study sites. All mothers to be included in the study must have been registered by the VHT at the household level in this household register.The ttC register (ttCR): This will provide the data required for the intervention implementation analysis (process evaluation). It will also be the entry point for mothers to be included in the study and the VHTs are responsible for documentation using this register. The tool captures day-to-day visit activities between the household and the VHT.Study Questionnaire (SQ): This has been developed specifically to collect data that will be used for outcome results at the end of the intervention. An expert staff member in ttC has provided guidance that led to the revision of the tool in line with the sub-objectives. Furthermore, two researchers were asked to critically review the tool in line with the standard objectives. Their comments have been incorporated into the tool. More pre-testing of the tool will be done at the field level during the training of the enumerators.

These instruments and the variables assessed are described in more detail below.

### 2.12. Study Variables

The suggested tools above will be used to collect data on the variables in Table 4 below:

## 3. Data Management and Analysis

The data from the previous day of the study is entered and cleaned immediately, enabling immediate feedback on any issues to the data collection team. Once the team responsible for the tool returns from the field, brief conversations will be done to ensure that data was not missed at collection level.

Under the guidance of the statistician, a data entry template will be created using the expanded program of immunization info. All data shall be entered using this data entry template. Tools at data collection will be given a unique code. The process of unique coding will include sub-county, parish, village and then household number following the sampling frame. To ensure that each tool has a unique number, data collectors will be assigned numbers to use before heading into the field.

The data after entry is the responsibility of the statistician and the investigators at analysis. This data shall be attached to all publications for the world to have access to. This excludes personal data.

Univariate analysis will be done using SPSS, considering all data that requires a unilateral representation from the study. Baseline data as well as key demographic information from both comparison and implementation sites will be examined.

Several exploratory tests will be done to evaluate the data for dependencies and possible violations of normality and other key assumptions. Bivariate analysis will be used to determine the empirical relationship between study variables. This includes the differences between the implementation and comparison areas. In addition, the relation between the statuses at the baseline and the status of the indicators with a focus on the contribution of ttC will be examined. Next, multivariate analyses will be conducted, adjusting for potential relevant confounders (such as the implementation of a birth plan and a fourth ANC attendance (or more) on clean birthing practices). Depending on preliminary analyses, either fixed or random effects models will be selected for subsequent multivariate analysis, adjusting for the multi-level structure of the data, caused by the clustering of participants within villages.

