### 2.8. Sample Size

The sample size is calculated using the formula for comparing differences in rates and proportions between two groups and determining the number of subjects per group^n^, using an individual binary for a two-sided significant level α and power 1-β [27]. With an anticipated effect size of 10% [δBinary = (^μ^T − ^μ^C)], α = 0.05 (two-sided), β = 0.2,^ z^1^−α^/2 = desired significance level at 95% (0.05). ^Ζ^1 − β = desired power at 80% (0.842), type of test = two-sided, and absolute risk reduction = 10%.

Since the study focuses on uptake of pregnancy services and essential newborn care, the key participants are pregnant mothers. We, therefore, estimate the pregnancy rate from each area using the 2020 population estimates per district, then turning the pregnancy rate into a percentage proportion. To estimate pregnancy rate, the focus will be on the recommended women of reproductive age within the population. Using the health care planning estimation, it is estimated that 24% of the population are women of reproductive age [28]. An estimation of number of births, abortions and foetal losses was acquired from the actual total 2019 health management and information systems [29] reports for both districts. This provided a 1107-sample size in the two districts. This will be increased by 10% to 1218 participants to cater for a non-response. Therefore, the treatment and control groups will each have 609 mothers at the end of the study.

To determine number of clusters needed (n_cluster) [27,30]: n _cluster = total number of participants in the two groups (/fixed cluster size) which is (^n^Cluster_Binary 2)/m = 1218/60, giving us 20 clusters. In order to have the same number of clusters per arm, the number of clusters will be increased to the nearest upper even number, which is 20 in this study. This means that the sample size contains 1218 pregnant mothers in 20 clusters which is the sub-county by the administrative units of Uganda [31].

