### 2.10. Sampling Procedure

A multi-stage sampling technique will be employed to select study participants. A total of 20 clusters of sub-counties will be selected and included in the study, based on the power calculation. Sub-counties with largest numbers of pregnant mothers registered by the VHTs will be included to ensure that the estimated study sample size is met. This will be used to increase the level of efficiency of sampling and each cluster will be considered as a sampling unit. At the beginning of the study, the team will consult the ttC registers from the VHTs in Hoima and the VHT registers from Masindi to assess the pregnancy registration per sub-county. For each sub-county, six villages will be randomly selected, with each village providing 10 households.

At the household, selection of pregnant mothers to be included in the study will be done systematically. In this probability sampling, participants will be selected from a larger population of pregnant mothers according to a random starting point and a fixed periodic interval. This periodic interval will be determined beforehand as two, which means that assuming the starting point is one as the first serial number on the VHT register, every pregnant mother with an even serial number will be selected to participate in the study, that is, 2, 4, 6, 8, etc. The sampling procedure is presented in Figure 3.

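### Section 3 puts the comparison of the two areas in the bivariate step but states the clustering adjustment only for the later multivariate step, so the bivariate results, read as written, would look too precise

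*Protocol article*

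**What the plan says.** Section 3 of the Protocol article sets out an ordered analysis: univariate description, exploratory checks (including checks for dependencies), bivariate analysis, then multivariate analysis. Of the bivariate step it says: "This includes the differences between the implementation and comparison areas". Clustering enters only afterwards, where fixed or random effects models are to be chosen for "subsequent multivariate analysis, adjusting for the multi-level structure of the data, caused by the clustering of participants within villages". No bivariate test or standard-error method is named.

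The Abstract lists univariate, bivariate and multivariate analyses together as the means of assessing intervention effects on outcomes. It does not mark the bivariate part as descriptive.

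Section 2.8 defines the cluster as the sub-county, with 20 clusters and a fixed size of 60. Section 2.10 says that "each cluster will be considered as a sampling unit" and draws six villages per sub-county and 10 households per village. Section 2.2 gives the intervention to one district and usual care to the other. The note to Table 3 says that the end-term review compares the two areas, without saying by which analysis.

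**The concern.** Women in the same sub-county share health facilities, supervision and local practice, so their outcomes are likely to be correlated. A comparison of the two areas that uses the variance for independent women then understates the standard error. Section 3 says which step receives the clustering adjustment, and it is not the step in which the section places the area contrast. The planned check for dependencies does not close the gap. The only consequence that section 3 draws from preliminary analyses is the choice between fixed and random effects in the multivariate model.

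At stake is how the bivariate results are read. If they are published with p-values as evidence on ttC, ordinary variation between sub-counties can pass for an intervention effect. Section 3.1 intends the findings to be taken to the Ministry of Health for use elsewhere in the country.

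**Working it through.** **1. Does the sample size reveal a design effect?** Section 2.8 gives "α = 0.05 (two-sided), β = 0.2" and an absolute difference of 10 percentage points, but no rate for either arm. The usual formula per arm is

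n = [1.96·√(2·p̄(1−p̄)) + 0.842·√(p₁(1−p₁)+p₂(1−p₂))]² / δ²

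It is largest at 45% versus 55%: (1.96·√0.5 + 0.842·√0.495)² / 0.01 = (1.386 + 0.592)² / 0.01 ≈ 391.4. Rounded up this is 392 per arm, or 784 in total (824 with continuity correction). The article states: "This provided a 1107-sample size in the two districts". That figure does not follow from the stated inputs: 1107/784 = 1.41, and nothing explains the factor. The next steps do reproduce: 1107 × 1.10 = 1217.7, rounded to 1218, or 609 per arm; 1218/60 = 20.3, taken as 20 clusters. No ICC or design effect is stated, and none can be recovered from these numbers. The ICC below is therefore an assumption, shown over a range.

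**2. True type I error of a test that ignores clustering.**

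Inputs from the article: two-sided 5% level; m = 60 women per sub-county, 10 sub-counties per arm (section 2.8); m = 10 per village, 20 × 6 = 120 villages (section 2.10). Assumed: ICC from 0.001 to 0.10, equal cluster sizes, no true difference and no variation between districts.

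Design effect: DE = 1 + (m − 1) × ICC. 
Type I error: 2 × [1 − Φ(1.96/√DE)].

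Sub-county, ICC 0.05: DE = 1 + 59 × 0.05 = 3.95; √3.95 = 1.99, so the naive standard error is too small by a factor of about 2; 1.96/1.99 = 0.986; error = 0.324.

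Village, ICC 0.05: DE = 1 + 9 × 0.05 = 1.45; √1.45 = 1.20; 1.96/1.204 = 1.628; error = 0.104.

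| Assumed ICC | DE, sub-county (m = 60) | Type I error | DE, village (m = 10) | Type I error |
|---|---|---|---|---|
| 0.001 | 1.059 | 5.7% | 1.009 | 5.1% |
| 0.01 | 1.59 | 12.0% | 1.09 | 6.1% |
| 0.02 | 2.18 | 18.4% | 1.18 | 7.1% |
| 0.05 | 3.95 | 32.4% | 1.45 | 10.4% |
| 0.10 | 6.90 | 45.6% | 1.90 | 15.5% |

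**3. Check by simulation.** Beta-binomial data, 20,000 runs per setting, assumed base rates of 30% and 60%. At ICC 0.05 the naive test rejected in 33.1% and 32.6% of runs for 10 sub-counties of 60 per arm, and in 10.3% and 10.2% for 60 villages of 10 per arm. These agree with the formula. In a further simulation at a 60% base rate, a t-test on sub-county proportions (18 degrees of freedom) rejected in 5.1%, 5.0%, 4.9% and 5.3% of runs at ICC 0.01, 0.02, 0.05 and 0.10. It holds the nominal level there because the simulation contains no variation between districts.

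**The case against.** The strongest reply is that the article never says women are treated as independent. It names no bivariate test, it plans checks for dependencies first, and a condensed article may leave the variance method to a fuller document. This stands in part. That the bivariate comparisons ignore clustering is inferred from where the adjustment is placed, and is not a stated instruction. The inference is still a fair one, because the article is not merely silent: it assigns the adjustment to a particular step.

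A second reply is that crude comparisons followed by an adjusted clustered model are an ordinary order of work, and that nothing makes the bivariate comparison primary. That also stands, and it lowers the weight of the point. It does not remove it, since the Abstract includes bivariate analysis among the ways of evaluating effects.

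Third, the size depends on an assumed ICC and on the level to which it applies. Section 3 names only villages, for which the inflation is much smaller. This is correct, and both levels are therefore shown. Sections 2.8 and 2.10 define the cluster as the sub-county, so the village figures alone would not represent the design.

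A reader might also infer that the bivariate step is the only place where the two areas are compared. The article does not support that: the Table 3 note also names an area comparison, and the multivariate analysis is counted as an effect analysis too.

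**Conclusion.** The point holds as a matter of clarification and correction in section 3. Following the sequence as written gives area comparisons, counted among the effect evaluations, whose uncertainty is understated. Over the assumed ICC range of 0.001 to 0.10, the true error of a nominal 5% test would be about 6% to 46% with sub-county clustering and about 5% to 16% with village clustering only. Any positive ICC inflates it; how much is not known from the article.

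Two stronger readings should be resisted. One is that the plan has a one-in-three false-positive rate. That is a single scenario (ICC 0.05 at sub-county level), not a property of the plan. The other is that the study's conclusions on ttC must rest on uncorrected tests. A multivariate step that allows for clustering is stated, so the misleading results would be the bivariate ones, if they are reported as tests of effect.

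**What to change.** Add one sentence to section 3: bivariate comparisons of the two areas either (a) account for sub-county clustering, by a t-test on the 20 sub-county proportions or means or by a model with sub-county random intercepts and small-sample degrees of freedom, or (b) are reported descriptively, without p-values. In the same edit, reconcile the village clustering named in section 3 with the sub-county cluster of sections 2.8 and 2.10.

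The cost is small. Section 3 already builds the sub-county into each unique code, so no new data are needed. The price is wider intervals and, under (b), no bivariate tests of the area difference.

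The change corrects for sub-county clustering only. With one district per arm, a sub-county analysis keeps its nominal error rate for a ttC effect only if the districts would not otherwise differ. Section 3.2 should state as a limitation that district differences remain confounded with ttC.

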## Abstract

Background: Although mortality rates have declined in Uganda over the last decade, maternal mortality is still high at 336 deaths per 100,000 live births, as is infant mortality at 43 deaths per 1000 live births. One in every 19 babies born in Uganda does not live to celebrate their first birthday. Many of these deaths occur within the first 28 days of life, forming the single largest category of death. Promising effects for preventing death are expected from timed and targeted counselling (ttC), an intervention package of key messages and actions that address integrated health and nutrition needs of the mothers and children, barriers and negotiation agreement, to cause sustainable behavioural change at specific timelines in the first 1000 days. Methods: The study has a quasi-experimental design in order to evaluate the implementation and effectiveness of the ttC intervention. Participants are pregnant women who have been registered by village health team (VHT) members and who live in Hoima (intervention region) or Masindi (control region) districts, who will be monitored throughout their pregnancy up to at least six weeks after delivery. A multi-stage sampling technique will be employed to select participants, the study sites being purposively chosen. Sample size is determined using the pregnancy rate from the population estimates, resulting in a total required sample of 1218 (609 each in the intervention and control group). Study instruments that will be used include the Ugandan VHT household register (in which all mothers to be studied will be registered), the ttC register (an additional tool for the study area), and a study questionnaire, to collect data at outcome level. Univariate, bivariate and multivariate analyses will be performed using SPSS to evaluate intervention effects on outcomes (e.g., relationship between pregnancy outcomes and antenatal attendance). In addition, quantitative findings will be triangulated with qualitative data, and collected through interviews and focus group discussions with participants and implementers. Discussion: The proposed study will examine the effectiveness of implementing ttC to improve maternal and child outcomes in Uganda. If ttC is effective, broader implementation of appropriate antenatal services can be advised as essential newborn care improvements. Trial registration: PACTR, PACTR202002812123868. Registered on 25 February 2020.

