The Ugandan strategy [4] of implementing the VHT at the household level aims to promote the health and wellbeing of all village members. The coverage of each VHT is at least 30 households. The role of VHTs [12] includes the mobilization of village members for health activities mainly organized by the health centres in the area, keeping village health records up to date, making monthly village health reports and organizing meetings for the village members to provide an update on the current health status for that particular village. The VHT promotes health to prevent disease, reports village sickness to health workers, performs periodic checks for danger signs in village members who are sick, and focuses on maternal newborn and child health (MNCH) services affecting behavioral change.

Timed and targeted counselling (ttC) [13] is a package of key MNCH messages and actions that are disseminated and passed on to pregnant and breastfeeding mothers, aimed at achieving sustainable behavioural change at specific time points within the first 1000 days of a child’s life. The strategy also targets key decision makers in households (e.g., husbands, grandmothers). The approach addresses integrated MNCH needs of the target groups, barriers, and negotiation of agreements with household decision makers on issues affecting the women. Targeted pregnancy outcomes refer to timely goal-oriented ANC, birth preparedness, male involvement, and delivery at a health facility, which are considered as contributing to appropriate birth outcomes. Targeted outcomes are related to a newborn survival focus on the first 28 days of life: cord care practices, essential newborn care, male involvement, and immunization as a contribution to the growth and development of the baby. The current paper describes the protocol for a study examining whether the implementation of the ttC intervention improves pregnancy outcomes and newborn survival in rural Uganda. Our hypothesis is that ttC has a positive effect on both pregnancy outcomes and newborn survival.

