### 2.5. Conceptual Framework

The proposed study aims to determine the effect of ttC on pregnancy outcomes and newborn survival in rural Uganda. Specifically, the study aims to ascertain the extent to which ttC improves uptake of timely goal-oriented ANC with a focus on the recommended visits, and to determine whether ttC contributes to the recommended hygienic birth practices. Additional aims are to establish the extent to which ttC improves essential newborn care practices during the newborn period, and to ascertain the extent to which ttC fosters positive male involvement in pregnancy and newborn care. Finally, the study aims to ascertain the relationship between ttC implementation and appropriate pregnancy weight gain by end of pregnancy and appropriate birth weight.

We expect that if the VHTs implement ttC effectively, there will be an increased uptake of ANC services in the intervention districts, including the timely attendance of goal-oriented ANC services, and the development and implementation of a birth plan. In addition, we expect essential newborn care improvements at the levels of the health facility and the community, aimed at newborn survival within the first 28 days of life, as well as improved visible male involvement in MNH care, including escorting the pregnant women for at least one ANC where couple human immunodeficiency virus (HIV) counselling and testing occurs. Ultimately, we expect these improvements to result in appropriate pregnancy outcomes and newborn survival (see Figure 1).

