No	Variable	Description of Variable	Tool to Be Used
Dependent Variables			
1	Appropriate pregnancy weight gain at end of months pregnancy	Pregnancy weight gain of 11.5 kg to 16 kg by the end of the pregnancy	SQ
2	Newborn morbidity within the first 28 days of life	Newborn morbidity (focusing on cord infections, sepsis, asphyxia, fever, common flu and cold and diarrhea, pneumonia) within the first 28 days of life	SQ and ttCR
3	Appropriate birth weight	Appropriate birth weight of 2.5 kg or more	SQ
4	Mortality of newborns and mothers	If the mother died during pregnancy or childbirth, if the baby died either during pregnancy, childbirth or within the first 28 days of life.	SQ and ttCR
5	Overall maternal wellness	During pregnancy or newborn period, a mother does not develop sepsis, urinary tract infections, obstruction during birth or any danger signs during this period.	SQ and ttCR
Independent Variables			
1	Uptake of timely goal-oriented ANC	With a focus on the recommended four visits, the associated recommended services offered during these visits and timeliness of attendance.	VHTR, SQ and ttCR
2	Clean birthing practices	Birth attended by a skilled health provider, delivery happened in a health facility and a mama kit was used during the process.	SQ and ttCR
3	Essential newborn care practices (ENC) during the newborn period	Early initiation of breastfeeding, cord care practices, baby thermal care, sustained breastfeeding and baby WASH practices.	SQ and ttCR
4	Positive male involvement in pregnancy and newborn care	Man participates in at least one ANC, does an HIV test with the mother, available during birth, supports mother to help her rest, contributes finances for related logistics.	SQ

Notes: SQ: Study questionnaire, ttCR: ttC register, VHTR: Ugandan VHT household register.

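### Birth-plan implementation and four or more ANC visits are named as confounders for clean birthing practices, although ttC is meant to change both, so adjusting for them removes the part of its effect they carry

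*Protocol article*

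**What the plan says.** Section 3 (Data Management and Analysis) plans descriptive analysis, then bivariate analysis that includes differences between the two areas, then multivariate models "adjusting for potential relevant confounders (such as the implementation of a birth plan and a fourth ANC attendance (or more) on clean birthing practices". No other covariate is named. The abstract gives the purpose: "Univariate, bivariate and multivariate analyses will be performed using SPSS to evaluate intervention effects on outcomes".

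Elsewhere the article treats the same two variables as results of the intervention:

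- Section 1 (Background): "Targeted pregnancy outcomes refer to timely goal-oriented ANC, birth preparedness, male involvement, and delivery at a health facility".
- Section 2.5 expects higher ANC uptake where ttC is delivered, "including the timely attendance of goal-oriented ANC services, and the development and implementation of a birth plan".
- One specific aim in section 2.5 is to "ascertain the extent to which ttC improves uptake of timely goal-oriented ANC with a focus on the recommended visits". Cleaner births as a result of ttC are a further aim there.
- Table 1: the visit at four months checks that the woman has been to ANC and urges the next attendance. The visit at six months deals with the birth plan.

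Table 4 defines clean birthing practices as a skilled attendant, a facility delivery and use of a mama kit. It places them, with "Uptake of timely goal-oriented ANC", under independent variables.

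**The concern.** A confounder of the ttC comparison must influence the outcome and differ between the districts for reasons other than ttC. A variable that ttC itself changes, and that then changes the outcome, is a mediator. With mediators in the model, the ttC coefficient no longer answers whether the programme improves clean birthing. It answers whether the programme does so by routes other than the mediators.

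This matters more here than in a randomised trial. Two purposively chosen districts are compared, so an unadjusted difference is open to confounding and readers will tend to rely on the adjusted result. Section 2.2 itself reports a difference in households 5 km or more from a health facility (39.5% in Hoima, 29.5% in Masindi). If the adjusted model contains the two mediators, the effect of ttC on clean birthing would be understated in the analysis most likely to be believed.

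**Working it through.** **Causal order, from the article alone**

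1. Exposure: ttC is assigned by district (sections 2.1 and 2.2) and delivered through timed home visits from early pregnancy (Table 1).
2. Next: ANC attendance and the birth plan, both promoted at those visits and both expected to rise (section 2.5, Table 1).
3. Last: clean birthing practices, which are fixed at delivery (Table 4) and are themselves a ttC aim (section 2.5).

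Both covariates therefore fall after the exposure and before the outcome. The article attributes changes in them to ttC, so they lie on the path.

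**Size**

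The article states no figure to reproduce and no effect of ttC on either variable. What follows is an illustration, and every input is an assumption:

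- dM, ttC effect on attendance at four or more ANC visits: 10 to 20 points
- dB, ttC effect on birth-plan implementation: 10 to 30 points
- gM and gB, effect of each on the probability of a clean birth: 20 to 30 points, taken as equal
- D, effect of ttC by any other route: 0 to 5 points

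The model is additive in risk, with no interaction and no unmeasured common cause of mediator and outcome:

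- total effect = D + gM×dM + gB×dB
- ttC coefficient after adjustment for both = D
- share removed = 1 − D / total

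The indirect part runs from 0.20×0.10 + 0.20×0.10 = 0.04 to 0.30×0.20 + 0.30×0.30 = 0.15.

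| D (points) | Total effect (points) | Adjusted coefficient (points) | Share removed |
|---|---|---|---|
| 0 | 4 to 15 | 0 | 100% |
| 2 | 6 to 17 | 2 | 4/6 = 67% to 15/17 = 88% |
| 5 | 9 to 20 | 5 | 4/9 = 44% to 15/20 = 75% |

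One case in full: dM = 20, dB = 30, gM = gB = 20 and D = 2 points give a total of 2 + 4 + 6 = 12 points. The adjusted coefficient is 2 points, so 10/12 = 83% is removed.

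The 44% to 100% range is not a bound. If the smallest assumed contrasts are halved (dM = dB = 5 points) with gM = gB = 20 and D = 5, the indirect part is 0.20×0.05 + 0.20×0.05 = 0.02. The share removed is then 2/7, or about 29%. A small contrast in ANC attendance is conceivable, because Table 2 has control-district VHTs supporting ANC attendance and making four visits as well.

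**The case against.** **Narrow scope.** The two variables are introduced as examples and tied to one outcome. Nothing says they will enter models for birth weight, morbidity or mortality. This stands and limits the point to clean birthing practices. It does not rescue the examples: they show what kind of variable is to be treated as a confounder, and both are of the wrong kind.

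**Ambiguous wording.** The sentence does not name ttC as the regressor. It could be a compressed description of a model in which ANC and birth plan predict clean birthing, which would fit Table 4. That reading is possible, but the abstract ties the multivariate analyses to intervention effects. Even on that reading, confounder is the wrong word and the analysis needs a different label.

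**An unadjusted comparison is also planned.** This is true, and it keeps the total effect. A reader might infer that an effective programme is bound to be reported as having no effect. The article does not support that, because the bivariate result would also be available. It offers no control of confounding, however.

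**Other routes exist.** A reader might infer that adjustment removes the whole effect. Table 1 speaks against this: visits 2 and 4 promote facility birth directly, and visit 4 covers the clean birthing kit. Both are components of the outcome. The 100% row in the table above follows only from assuming no other route.

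**Further bias from shared causes.** Unmeasured causes common to ANC attendance and facility birth could also distort the remaining coefficient. This is a general possibility. The article gives nothing to size it, no calculation here covers it, and the point does not rest on it.

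**Table 4 and the abstract's example.** A reader might see the independent-variable heading, or the abstract's example ("evaluate intervention effects on outcomes (e.g., relationship between pregnancy outcomes and antenatal attendance"), as the same error repeated. Table 4 lists variables and instruments and prescribes no adjustment. Its labels can follow the chain in section 2.5, from behaviours to health outcomes. ttC is set by district, so its absence from a list of collected items is no analytic fault. What remains is a labelling inconsistency with the aims in section 2.5.

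**Conclusion.** The article contradicts itself. Section 3 calls birth-plan implementation and four or more ANC visits confounders for clean birthing practices, while the Background, section 2.5 and Table 1 make both intended effects of ttC. If the ttC comparison is adjusted for them, the part of the effect they carry is lost and only a direct effect remains.

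The direction follows from the text, provided that ttC works as the article expects and that the sentence describes a model for the ttC effect. The size cannot be derived from the document. Under the assumed ranges it is roughly 44% to 100% of the effect, and less if ttC moves the two variables only slightly. The conclusion concerns one outcome and the adjusted analysis only. It does not show that the whole effect disappears, or that other outcomes are affected.

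**What to change.** In section 3:

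- Remove birth-plan implementation and ANC attendance from the adjustment set for the effect of ttC.
- Adjust that comparison only for variables fixed before exposure that the study already collects, drawn from the baseline and demographic data mentioned in the same section, and name them.
- Label any model with ANC attendance or birth plan as a regressor a secondary mediation or association analysis.

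At Table 4, add a note that the four behaviours listed as independent variables are outcomes when the effect of ttC is estimated, in line with the aims in section 2.5.

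The cost is chiefly wording; sample size, visits and instruments are untouched. One check is needed first. The article does not list the individual demographic items, so whether parity, literacy or distance to a facility is recorded for each woman cannot be confirmed from it. The illiteracy and distance figures in section 2.2 are district percentages. With one district per condition they coincide with the exposure and cannot serve as adjustment variables.
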